### Measures of other outcomes

For the first set of additional outcomes used in this study, the following measures are used.

• The FES is a scale adapted and expanded by the authors from the High-K Strategy Scale (HKSS) [50]. The HKSS has been shown to be negatively associated with depressive symptomatology [25] and psychopathology in general [23]. The FES consists of 45 items (58 if the patient has children), tapping into various dimensions theorized to make up the indicators of fitness. Participants rate every item on a five-point Likert scale. A total FES score is computed by adding up ratings for each item, with higher scores indicating greater fitness. The FES was preliminarily validated on a sample of 146 subjects, and showed good internal consistency (Cronbach’s α = 0.93). The FES is the therapist’s starting point in prescribing the evolutionary-driven interventions, as further detailed below.

• The Mate Value Inventory (MVI) [26] is a multivariate assessment of attributes desired in the self, and in social or sexual partners.The MVI is a list of 17 traits, for which participants are asked, ‘How well do you feel that these attributes apply to you currently,’ and are measured on a scale of -3 (extremely low on this trait) to +3 (extremely high on this trait). These traits are: ambitious, attractive face, attractive body, desires children, emotionally stable, enthusiastic about sex, faithful to partner, financially secure, generous, good sense of humor, healthy, independent, intelligent, kind and understanding, loyal, responsible, and sociable. Mate value is the summed score of these items. The MVI has been translated and adapted into Romanian for the purposes of the current study.

• The Components of Mate Value Survey (CMVS) [51] is a 21-item self-report measure. It is based on the Self-Perceived Mating Success Scale (SPMSS) [52], but in addition to the aspects of mate value indexed by SPMSS, it includes aspects related to sociality, parenting, wealth, looks, relationships history, and fear of failure. The CMVS has adequate reliability [26], and has been adapted into Romanian for the purposes of this study.

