• Behavioral Inhibition System/Behavioral Activation System (BIS/BAS) [53] is a 20-item self-report questionnaire that consists of a Behavioral Inhibition subscale (making up the BIS) and three Behavioral Activation subscales (making up the BAS). Each item is rated on a four-point Likert scale, from 1 (strongly agree) to 4 (strongly disagree). A number of studies have indicated adequate psychometric properties [54,55]. The BIS/BAS scales have been validated on the Romanian population in previous studies [55].

• The Physical Health Questionnaire (PHQ) [56] is a brief 14-item self-report scale used to assess frequency of somatic symptoms (gastrointestinal problems, headaches, sleep disturbances, and respiratory problems). Items 1–11 are rated on a seven-point frequency scale, ranging from 1 (not at all) to 7 (all of the time). Items 12–14 have different frequency-related responses, but the participant uses the same seven-point frequency scale. Higher mean scores reflect better somatic health. The PHQ has shown good psychometric properties [57-60], and has been translated into Romanian for the purposes of this study.

• The Santa Clara Strength of Religious Faith Questionnaire (SCSRFQ) is a brief, reliable and valid self-report measure assessing strength of religious faith and engagement, which is suitable for use with multiple religious traditions. It comprises 10 items, scored on a four-point Likert scale, with higher scores denoting increased levels of religious faith. The SCSRFQ has been widely used in medical, student, psychiatric, and general populations internationally, and has good psychometric properties [61-65]. The questionnaire has been translated and adapted into Romanian for the purposes of this study.

• Brief COPE (B-COPE) [66] is a 28-item brief form of a previously published measure called the COPE inventory [67], which has proven to be useful in health-related research. Respondents rate the items on a four-point Likert scale, from 1 (I haven’t been doing this at all) to 4 (I’ve been doing this a lot). Scores are derived separately for two main categories of coping strategies, namely, ‘emotion focused’ and ‘problem focused’ coping. B-COPE has been successfully used on Romanian samples [40].

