• The Positive and Negative Affect Scale (PANAS) [68] is a 20-item self-report questionnaire, designed to assess mood. It distinguishes between positive and negative affect. Participants rate each item on a five-point Likert scale, from 1 (very slightly/not at all) to 5 (extremely) to indicate how they felt during the indicated timeframe. The PANAS can be used to assess mood on various time scales by altering the instructions. Possible time scales include moment, today, past few days, past week, past few weeks, past year, and general. For the purposes of this study, we used a 2-week interval. The validity and internal consistency of the PANAS are good, with test–retest reliability being the highest for the ‘general’ temporal instruction [68]. The PANAS has been used previously on the Romanian population, and was found to have adequate psychometric properties [69,70].

To explore the different mechanisms by which the two treatment approaches (ED-CT and CT) might lead to improvement (that is, the second set of additional outcomes), the following measures are administered.

• The Automatic Thoughts Questionnaire (ATQ) [71] is a 15-item self-report measure used to assess depression-related cognitions. Participants rate on a five-point scale, (from 1 (never) to 5 (almost all the time)) how frequently they have had a given thought over the past week. A higher score shows a higher frequency of automatic thoughts. The psychometric properties of the ATQ have been adequately demonstrated in previous studies [72].

• The Dysfunctional Attitudes Scale (DAS) [73] is a 40-item self-report instrument which measures attitudes that, according to the cognitive theory of depression, contribute to vulnerability for depression. Participants rate on a seven-point scale, from 7 (total disagreement) to 1 (total agreement), the level of personal concordance with the item presented. The higher the score, the more dysfunctional the participant’s attitudes. Adequate internal consistency and test-retest reliability for DAS have been reported in the literature [74].

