### Dissemination policy

The principal investigator and the research team intend to publish the trial results in a peer-reviewed journal, focusing on two main areas: 1) primary outcomes results and 2) mechanisms of change results. Presentations at international conferences on the topic are also envisioned. Furthermore, the intervention manual will be sent out for publication, and will be made available upon request from the first author.

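### FES totals are not comparable between parents and non-parents, and the stated PHQ and DAS codings do not fit their stated score directions (minor; exploratory outcomes only)

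*Protocol article*

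**What the plan says.** All three scoring rules are in the protocol article, under Measures of other outcomes.

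- **FES.** "The FES consists of 45 items (58 if the patient has children"). "Participants rate every item on a five-point Likert scale", with no numeric anchors given. "A total FES score is computed by adding up ratings for each item, with higher scores indicating greater fitness". No averaging, pro-rating or common-item score is mentioned.
- **PHQ.** It "is a brief 14-item self-report scale used to assess frequency of somatic symptoms". Items 1–11 are rated on seven points "ranging from 1 (not at all) to 7 (all of the time"), and items 12–14 use the same seven-point scale. The direction is given as "Higher mean scores reflect better somatic health".
- **DAS.** Its 40 items measure attitudes held to make a person vulnerable to depression. Patients rate, "from 7 (total disagreement) to 1 (total agreement), the level of personal concordance with the item presented". A higher score is then said to mean more dysfunctional attitudes.

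The same section does state a reversal for the ABS II, where rationally worded items are reverse scored. It states none for the FES, PHQ or DAS.

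The Other outcomes section places FES and physical health in a first exploratory set, used among other things to see whether any ED-CT advantage goes with gains in fitness. It places DAS in a second set, on presumed cognitive mechanisms. The Dissemination policy names "mechanisms of change results" as one of two areas for publication.

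**The concern.** A sum over different numbers of items is not one scale. Two patients who answer the 45 shared items identically can get different totals only because one has children, so a higher total does not reliably mean greater fitness across patients. The size of a change also depends on parenthood. This matters most when FES change is related to depression outcome, because that association is not protected by randomisation.

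For PHQ and DAS the question is whether the printed coding can produce the printed direction. If it cannot, a reader or programmer who follows the text literally would read an improvement as a deterioration, or the reverse.

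**Working it through.** **The plan's own figure.** The scoring rules come with no computed figure. The only design figure is N = 100 (Sample size section: f = 0.247, two groups, two measurements, correlation 0.50, α = 0.05, power 0.80). With λ = f²·N·m / (1 + (m − 1)ρ) = 0.247² × 100 × 2 / 1.5 = 8.13 and df (1, 98), power is 0.806, and 100 is the smallest even N that reaches 0.80. The figure reproduces and does not depend on these scales.

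**FES level.** Inputs from the document: 45 and 58 items, hence 13 extra; five response points. Assumed: coding 1–5, with 0–4 as the alternative.

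| | 45 items | 58 items | Gap at mid rating |
|---|---|---|---|
| 1–5: range | 45–225 | 58–290 | |
| 1–5: mean rating 3 | 135 | 174 | 13 × 3 = 39 |
| 0–4: range | 0–180 | 0–232 | |
| 0–4: mean rating 2 | 90 | 116 | 13 × 2 = 26 |

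With 1–5 coding, a parent averaging 180/58 = 3.10 per item has the same total as a non-parent averaging 4 (45 × 4 = 180). A parent who gives all 13 parent items the lowest rating still gains 13 points.

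**FES change.** The parenthood offset cancels in within-patient change as long as the patient's item set stays the same. The scale does not cancel: an equal change on every item is 58/45 = 1.29 times larger in a parent. This is an upper figure; if the parent items do not move while the others do, the ratio is 1.

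**Chance imbalance between arms.** Inputs: 43 and 57 patients (Sample size section) and simple unrestricted randomisation (Assignment to interventions). The proportion of parents, p, is not given; 20% to 70% is assumed.

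- SE of the difference in the proportion of parents = √[p(1 − p)(1/43 + 1/57)]. At p = 0.5 this is √(0.25 × 0.0408) = 0.101, so one SE is 0.101 × 39 = 3.9 FES points.
- The expected absolute difference is about 6 to 8 percentage points over this range of p, or about 2.5 to 3.1 FES points at the 39-point gap.
- A 20-point difference in the percentage of parents gives 0.20 × 39 = 7.8 FES points. At p = 0.5 that is 0.20/0.101 = 2.0 SE. The exact binomial probability of a difference at least that large is about 5% at p = 0.5, 3% at 0.3 or 0.7, and 1.3% at 0.2.

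**Added variance.** If half the patients are parents (assumed), the 39-point offset alone contributes a between-patient SD of 39 × √(0.5 × 0.5) = 19.5 points.

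**PHQ.** As printed, a patient with no symptoms has a mean of 1 and one with constant symptoms a mean of 7, so higher is worse. Recoding each item as 8 − x gives 7 and 1, which matches the stated direction. Keeping the coding and saying that higher is worse would be equally consistent.

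**DAS.** If all 40 items are worded as dysfunctional attitudes, full agreement scores 40 × 1 = 40 and full disagreement 40 × 7 = 280, so higher is less dysfunctional. Let k items be adaptively worded and none recoded. The most dysfunctional pattern then scores (40 − k) × 1 + 7k = 40 + 6k and the least dysfunctional 7(40 − k) + k = 280 − 6k. The stated direction needs 40 + 6k > 280 − 6k, that is k > 20, or at least 21 adaptively worded items. The document says nothing to suggest this.

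**The case against.** **Parents may be meant to score higher.** The rationale section ties fitness to reproductive success and lists parenting among the biosocial goals. This has some force: summing is not an arithmetic error, and the choice of total is partly scale design. But with 1–5 coding the sum rewards parenthood even when every parenting item gets the lowest rating, and it stretches change as well as level.

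**Keying is usually left to the instrument's source.** A condensed article need not print item keys, the final direction is stated for both scales, and the DAS item wording is not given. That stands as a reason to treat PHQ and DAS as possible errors of description. It does not remove the inconsistency: the article chose to print both anchors and direction, and they do not fit without an unstated step. The PHQ case is plain; the DAS case rests on the natural reading of the items as dysfunctional attitudes.

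**Stronger readings a reader might infer, which the document does not support:**

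- That parenthood confounds the ED-CT versus CT comparison on FES. It is balanced in expectation, and the offset drops out of within-patient change.
- That a spurious arm difference of 7.8 points is to be expected. It is roughly a 2-SE event.
- That PHQ and DAS results will have the wrong sign. That follows only if the printed anchors are used without keying, and nothing shows that they are. If every item were left unreversed, the label would flip but the effect size and p-value would not.
- That these three scales carry the mechanisms paper. The article ties mechanisms to ATQ, DAS, GABS and ABS II, so DAS is one of four; FES and PHQ belong to the other exploratory set.

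**Conclusion.** The point holds as a minor one.

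Raw FES totals cannot be compared between parents and non-parents. The gap at a mid rating is 39 points with 1–5 coding or 26 with 0–4, and an equal per-item change is up to 1.29 times larger in parents. The consequences are extra between-patient variance, a typical chance difference between arms of about 3 to 4 FES points (at the 39-point gap, with about half the sample parents), and distortion of exploratory analyses that relate FES to outcome.

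The PHQ description contradicts itself unless a reversal is applied. The DAS description does so unless items are reversed or at least 21 of the 40 are adaptively worded.

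The FES sizes rest on the assumed item coding and, for imbalance and variance, on an assumed proportion of parents. All three scales are exploratory; BDI-II, the SCID diagnosis, the secondary outcomes and the sample size are untouched.

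**What to change.** - **FES.** Define the total as the sum of the 45 items that everyone answers, and report the 13 parent items as a separate subscale. The alternative is the mean item score, which has the same range for everyone but assumes that the parent items behave like the rest. Either can be computed from data already collected; the cost is lost comparability with raw sums used so far.
- **PHQ and DAS.** Reconcile the printed coding and direction with the scoring keys, state which items are reversed, and correct whichever statement is wrong. Before analysis, run test records through the electronic scoring (no symptoms and constant symptoms for PHQ; the most and least dysfunctional answers for DAS) and confirm the direction. The cost is a sentence or two per scale and a short programming check.

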#### Participant timeline

For the study, potential participants are provided with verbal and written information during the first appointment with a clinical psychologist. Written consent for the participation in the clinical evaluation part of the study is sought at this time. A second appointment is scheduled, in which the respondents are evaluated clinically. If the inclusion criteria are met, written consent for participation in the treatment part of the study is obtained, within a 2-week interval.

The participants are then randomized by a research assistant to receive either: 1) ED-CT or 2) CT, without being informed about their group allocation (see flowchart in Figure 1). Randomization is performed *a priori* using a computer software package (http://www.randomizer.org). In addition, the clinical psychologists who perform the clinical assessment are blinded to the experimental condition through the entire duration of the study. Participants who do not meet the criteria for the study are referred to the Babes-Bolyai Psychological Clinic or to a psychiatric clinic in Cluj-Napoca.

**Figure 1 F1:**
[figure not shown]
**CONSORT flow diagram**[94]**showing subject allocation to the therapy conditions.**

### Sample size

An *a priori* power analysis based on a medium effect size estimation indicated that a total of 100 participants are needed (planned main statistical test is ANOVA (repeated measures, between factors); *f* effect size: 0.247; statistical power: 0.80; α error probability: 0.05; two groups, two main measurements (pre-intervention and post-intervention); correlation between repeated measures: .50). Power analysis was computed using the G*Power 3.1.6 program [95]. Consequently, we randomized a total of 100 participants. Following generation of the random numbers, we decided to use the first sequence of numbers for the participants’ allocation to the groups. This resulted in 43 participants randomized to the CT group, and 57 participants randomized to the ED-CT group.

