## Background

Depression affects around 350 million people worldwide, and is estimated to become the leading cause of disease burden globally by 2030 [1]. More than 30 million people are affected by depression in Europe alone, and the associated annual costs are estimated at €92 billion [2].

There are several existing effective treatments for depression, including cognitive behavioral therapy (CBT) [3-5], interpersonal therapy (IPT) [6-10] and antidepressants [11].

CBT is the psychological standard of care for depression recommended as the first-line psychotherapeutic intervention [12]. In CBT, the root of the depressive symptoms is seen as a set of dysfunctional core beliefs/schemas, which distort information processing, thus leading to systematic negative cognitive biases [3-5]. In CBT, the therapist tries to modify these dysfunctional beliefs, as well as engage the patient in rewarding activities.

IPT for depression focuses on ameliorating interpersonal difficulties and emphasizes the role of social support in the onset and maintenance of depression. The treatment rationale in IPT is that improvement in interpersonal relationships leads to improvement in depressive symptoms, which positively feeds back onto interpersonal functioning [13]. Like CBT, IPT is one of the recommended treatments of choice by the National Institute for Clinical Excellence [12] and the National Institute of Mental Health [14].

Research on the efficacy of the therapies for depression shows that 30% to 50% of the patients do not respond to anti-depressive medication [11], and around 40% of patients with moderate to severe depression do not respond well to CBT [15]. Moreover, 40% of those patients whose depression does remit will relapse within 2 years [16] and 20% are at risk of developing chronic, unremitting depression [16,17]. Generally, meta-analyses indicate that all *bona fide* (non-placebo) psychological treatments for depression are equally efficacious [18], and the effect sizes of psychotherapy for adult depression vary from small to moderate [19].

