### Trial design

This study is designed to be a blinded, randomized, superiority clinical trial. The experimental group receives ED-CT, while the control group receives CT. We hypothesize that, because the intervention array is larger in the case of ED-CT, the therapeutic gains will be larger in this condition than in the CT group at the completion of the therapy, and that this will be maintained at the 3-month follow-up.

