The severity of, and improvement in the BDI-II scores within and between the groups will be examined using mixed-effects linear regression analysis with a random intercept and slope over time (four assessments: baseline, after sessions 4 and 8, post-treatment) and fixed effects for treatment assignment.) The 3-month follow-up data will be analyzed in a separate mixed-effects model. The main analysis will compare groups in terms of depression level (that is, diagnostic status and symptom intensity). Results on the other measures will be investigated in an exploratory manner. When analysis of secondary/other outcomes are performed, the error probability will be adjusted according to the number of group comparisons performed [98].

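### The 80% power is computed for a group difference in the pre/post average, so the assumed effect is about 0.99 SD at post-treatment rather than medium, and the analysis section plans a different model

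*Protocol article*

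**What the plan says.** All places are in the protocol article.

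- **Sample size.** The section states "power analysis based on a medium effect size estimation indicated that a total of 100 participants are needed". The test is given as "planned main statistical test is ANOVA (repeated measures, between factors", with "effect size: 0.247; statistical power: 0.80; α error probability: 0.05", two groups, two measurements (pre and post) and a correlation of 0.50. Unrestricted randomisation then gave 43 patients to CT and 57 to ED-CT.
- **Data collection, management, and analysis.** BDI-II scores are to be examined by "mixed-effects linear regression analysis with a random intercept and slope over time (four assessments: baseline, after sessions 4 and 8, post-treatment", with a fixed effect for arm and a separate mixed model for follow-up. The ANOVA does not appear here.
- **Trial design.** The hypothesis is that "the therapeutic gains will be larger in this condition than in the CT group at the completion of the therapy".
- **Primary outcomes.** Symptom level and diagnosis are both placed after treatment.

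**The concern.** In a two-occasion repeated-measures ANOVA, the between-factors effect is the group difference in the mean of the two occasions. Half of that mean is the baseline score, which is taken before any therapy and has the same expectation in both arms of a randomised trial. A treatment effect present only at the end of therapy is therefore halved in this contrast. The hypothesis and the primary outcomes concern the end of therapy, so the power was calculated for a contrast that answers a different question.

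The two sections also disagree about the main BDI-II analysis. If the ANOVA in the sample size section were run as declared, a real medium advantage of ED-CT would be missed about 7 times in 10. If the mixed model were run, the stated 80% would not describe it. Two declared analyses also leave room to choose between them once data are seen.

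**Working it through.** **Inputs from the Sample size section:** f = 0.247, N = 100, m = 2 occasions, r = 0.50, alpha = 0.05, allocation 43/57.

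**Assumptions made here:** zero expected baseline difference (from randomisation), equal pre and post SDs (varied in step 5), no attrition, no therapist clustering, and medium read as d = 2f = 0.494 SD at post-treatment.

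**1. Reproduce the stated figure.** For the between-factors effect, noncentrality = f² × N × m / (1 + (m − 1)r) = 0.061 × 100 × 2 / 1.5 = 8.13. With F(1, 98) the power is 0.806. N = 98 gives 0.798, so 100 is the smallest even total that reaches 80%. At 43/57 the power is 0.799.

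**2. Confirm which test it is.** The group-by-time option replaces the denominator with 1 − r and would need only N = 36. The stated 100 therefore comes from the between-factors option and is not loose wording for an interaction test.

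**3. Translate the effect to post-treatment.** If the difference is d at post and 0 at baseline, the difference in the average is d/2. Setting d/2 = 0.494 gives d = 0.988, about 0.99 SD.

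**4. Power for a post-treatment difference of 0.494 SD, 43/57, r = 0.50.** Noncentrality = (difference)² / variance × (43 × 57 / 100), where 43 × 57 / 100 = 24.51 and variances are in units of SD².

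| Contrast | Difference | Variance | Noncentrality | Power | d at post for 80% |
|---|---|---|---|---|---|
| Pre/post average (named ANOVA) | 0.247 | (1 + r)/2 = 0.75 | 1.99 | 0.29 | 0.99 |
| Change score, or two-occasion group-by-time | 0.494 | 2(1 − r) = 1.00 | 5.98 | 0.68 | about 0.57 |
| Baseline-adjusted (ANCOVA) | 0.494 | 1 − r² = 0.75 | 7.98 | 0.80 | 0.495 |

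**5. Sensitivity.**

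- *Correlation.* For r of 0.3, 0.5 and 0.7, the named test has power 0.32, 0.29 and 0.26, and the baseline-adjusted comparison 0.72, 0.80 and 0.92.
- *SD ratio.* Write k for baseline SD divided by post SD, with d in post SDs. The average then has variance (k² + 1 + 2rk)/4, which is 0.61, 0.5475 and 0.49 at assumed k of 0.8, 0.7 and 0.6. The named test has power 0.34, 0.37 and 0.41. The change score has 0.75, 0.78 and 0.79.

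**6. The mixed model in the analysis section.** The article gives no variance components, so these figures are illustrative. They assume d = 0.5 at post, linear divergence over the four assessments, equal variance at baseline and post, 43/57, and three splits of the variance that give a pre/post correlation of 0.5. A treatment-by-time slope then has power of about 0.71 to 0.73. A treatment main effect with no interaction has about 0.32 to 0.34, because it again averages over time.

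**The case against.** The strongest reply is that N = 100 survives. A baseline-adjusted comparison at 43/57 has power of about 0.80 for 0.494 SD. This stands, but it is a coincidence of the chosen correlation: (1 + r)/2 and 1 − r² both equal 0.75 at r = 0.50. The sample size section names no baseline adjustment, and at r = 0.3 the adjusted comparison has 0.72.

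A reader might infer that the trial has 29% power. The documents do not support that. The analysis section plans a different model, and a treatment-by-time contrast in it would have power near 0.7 under the assumptions above. The 0.29 applies only if the named ANOVA is run.

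A reader might also infer that the 0.80 corresponds to no planned analysis at all. That is too strong, because the sample size section itself calls the ANOVA the planned main test. The fault is that two sections name different main analyses and that the powered one does not fit the hypothesis.

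Two further cautions are fair. Entry requires a BDI above 13, which may narrow the baseline distribution, so 0.29 is the low end of the range over SD ratios (0.29 to 0.41). And the article does not say that its medium effect is a difference at post-treatment. That is the natural reading given the hypothesis and the primary outcomes, but it is a reading.

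Finally, the analysis section lists no treatment-by-time term. A condensed article may simply omit it, so the omission is not a separate fault. It does mean that the article leaves open which mixed-model contrast is intended.

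**Conclusion.** The point holds. The calculation is arithmetically right for the test it names, but that test compares the arms on the pre/post average. For the stated hypothesis, f = 0.247 on that average means about 0.99 SD at post-treatment, twice the 0.494 SD that the word medium suggests. For 0.494 SD at post-treatment the named ANOVA has power of about 0.29, or 0.34 to 0.41 if the baseline SD is 0.8 to 0.6 of the post SD. A change-score test has about 0.68 and a baseline-adjusted comparison about 0.80. Apart from the SD-ratio range, these figures assume equal SDs; all assume r = 0.50, 43/57, no baseline difference in expectation, no attrition and no clustering. The contradiction between the sample size and analysis sections rests on none of these assumptions. The finding does not show that the trial is too small. It shows that the stated power and effect belong to the wrong contrast, and that the main analysis must be made single and explicit.

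**What to change.** 1. Remove the between-factors ANOVA as the main test.
2. Name one main BDI-II contrast at post-treatment, in the same words in the sample size and analysis sections. A baseline-adjusted comparison is preferable (ANCOVA, or a longitudinal model with a common baseline). An explicit treatment-by-time contrast at post-treatment in the mixed model is also acceptable if power is stated for it.
3. Restate power for that contrast with its assumptions. For example: N = 100 (43/57), r = 0.50, two-sided alpha 0.05, 80% power for a post-treatment difference of 0.495 SD with baseline adjustment, before attrition and therapist clustering. With change scores the corresponding difference is about 0.57 SD.
4. If the between-factors ANOVA is kept, state that it has about 29% power for 0.494 SD at post-treatment, or that it detects about 0.99 SD with 80% power, under the same assumptions and equal pre/post SDs.

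The cost is wording in two sections. No additional patients or assessments are needed.
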